***Secondary outcomes***		
Outcome 3	Mortality (1 year)	Proportion of participants deceased within one year
Outcome 4 Outcome 5	Time to Readmission Days alive out of hospital	Proportional hazard model of readmission with a total duration of 1 year and median time to readmission estimated by Kaplan–Meier method Days spent alive out of the hospital within 30 and 90 days from discharge
Outcome 6	Clinical assessments/POCT measurements and their association to decision making	Regression analysis of the association between conducting a clinical measurement (e.g. Saturation, temperature, Sodium, CRP) or POCT analysis and the risk of readmission
Outcome 7	Costs associated with the intervention	Analysis of the costs associated with the intervention and potential savings from the result of the intervention
Outcome 8	User perspectives among involved participants and professionals	Analysis of questionnaires and focus group interviews with involved groups, including participants, community nurses, geriatric nurses, geriatric physician, and primary care physician

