**Methods:**

A single-centre two-arm parallel group randomised controlled trial using permuted block randomisation will be conducted. Randomisation occurs at discharge. The intervention consists of a follow-up visit within 2–5 days by a geriatric nurse and a community nurse. A systematic review of bodily functions is carried out, and solutions of identified problems are discussed taking into consideration the patient’s view. If the patient shows signs of worsened health since discharge vital status and bedside blood analyses using point-of-care-testing (POCT) can be carried out at the discretion of the geriatric nurse. As required the patients will be conferred with a senior geriatrician by video consultation. The patient’s primary care physician is invited to participate online. The control group will receive usual discharge. Endpoints are readmission, mortality rates and financial costs. User perspectives include focus group interviews with patients, geriatric nurses, community nurses, geriatricians and primary care physicians.

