At the visit, the participant, the geriatric nurse and the community nurse conducts a systematic assessment of the participant’s health and register any health-related problems. The assessment is conducted using a standardised Danish tool designed specifically for this purpose (Fælles Sprog III (FS-III) *(In English: Common Language III)*). Only a subsection of the tool, i.e. the parts covering mental well-being and bodily functions is used (“Helbredstilstande” (*In English: Health conditions*)). The tool is well known and used in the Danish home care system [35]. The Fælles Sprog III data is collected for the sole purpose of ensuring a systematic assessment.

For each item in the FS-III the geriatric nurse notes any changes in the participants’ health status, and whether the care plan has been followed, or deviations have been made. Adjustments to the care plan are made and noted accordingly. If there is any cause for concerns regarding the participant’s health compared to the time of discharge the geriatric nurse carries out vital status assessments. Further assessment by ultrasound bladder scan and/or bedside analyses of blood samples for C-reactive protein and electrolytes is based on the geriatric nurse’s clinical judgement. If the geriatric nurse finds it relevant, a geriatrician from G-OUH may be contacted by video. The geriatrician is thus able to communicate with the participant and the geriatric nurse, get the on-site clinically objective results, and finally make a clinical decision. If needed, the participant can be assessed the following day in the geriatric outpatient clinic or be acutely readmitted to the AMU.

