### Study outcome

The study outcomes are listed in the table below. Overall, we have several main focus areas:

The primary aim is to examine whether an early follow-up visit carried out simultaneously by a geriatric nurse and a community nurse can remedy a recently discharged participant’s health problems related to the hospital admission and reduce readmission. As such, the main outcome is 30 days acute readmissions. A readmission is defined as any hospital visit with a LOS of 12 h or longer, as this is in accordance with the definition of acute readmission by the Danish National Health Services [38]. Other aims include the use of in-home clinical assessment and use of POCT to understand their value in the clinical assessment, and their feasibility in an in-home setting. In addition, user perspectives on the home visit are a central outcome covering participants, community nurses, the geriatric nurses and the geriatrician. Other outcomes are the most common post-discharge health-related problems that arise or become apparent in the first days after discharge. Finally, health economic analysis will be carried out (Table 2).

**Table 2 Tab2:** Project outcomes

Outcome		Outcome measure

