### Data collection

Data will be collected at several points. The data will all be saved and stored in a secure database (REDCap). All personnel involved will be trained data collection.

Before the participant is invited to join the study, data is gathered on eligibility (i.e. diagnosed moderate to severe dementia, residence location to identify citizens of Odense Municipality, and type, use of home care, terminal diseases and presence of delirium).

Before discharge, data is gathered from the participants’ electronic medical records regarding discharge diagnoses, LOS, medication, medical history and Barthel ADL score [39]. A Clinical Frailty Score [40] is assessed by a geriatric nurse.

All data collected during the follow-up visit is registered in our database, including the data gathered in the FS-III survey, vital status and POCT results. The vital parameters and POCT results will be used to understand their influence on the clinical decision making.

The data collected during the follow-up visit will be filled directly into pre-defined fields in REDCap and will help ensure that all the necessary data is collected.

All participants, controls and interventions will receive a questionnaire, which is a modified version of a previously validated questionnaire [41]. At the time of randomisation, both groups will be asked about their satisfaction with the treatment, care and hospitalisation in general, as well as if they feel safe being discharged. A follow-up questionnaire will be administered to both groups by telephone. Data will be transferred to REDCap manually. The questionnaires will be administered by project coordinators who are not involved in the clinical care of the patients.

Data on death and readmissions will be collected from electronic medical records for 1 year after the allocation date for each participant.

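### Outcome 6 relates readmission to whether a test was done at the visit; because tests follow concern, the association is confounded by indication and cannot show the value of testing in either direction

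*Protocol article*

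**What the plan says.** Table 2 (Study outcome, secondary outcomes) names Outcome 6 "Clinical assessments/POCT measurements and their association to decision making" and gives its measure as "Regression analysis of the association between conducting a clinical measurement (e.g. Saturation, temperature, Sodium, CRP) or POCT analysis and the risk of readmission". The exposure is the act of testing and the response is readmission.

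Who gets tested is described in two places:
- Abstract, Methods: "If the patient shows signs of worsened health since discharge vital status and bedside blood analyses using point-of-care-testing (POCT) can be carried out", at the nurse's discretion.
- Intervention: "If there is any cause for concerns regarding the participant’s health compared to the time of discharge the geriatric nurse carries out vital status assessments". Beyond that, "bedside analyses of blood samples for C-reactive protein and electrolytes is based on the geriatric nurse’s clinical judgement", and the bladder scan falls under the same rule. The same section lists acute readmission among the possible results of the visit.

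The purpose is also given twice. Study outcome: "Other aims include the use of in-home clinical assessment and use of POCT to understand their value in the clinical assessment". Data collection: "The vital parameters and POCT results will be used to understand their influence on the clinical decision making".

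On adjustment, Analyses of primary and secondary outcomes promises known risk factors and gives multimorbidity, polypharmacy and length of stay as examples. Table 1 records all three at discharge. The structured health review at the visit (FS-III) notes change in health, but Intervention says that it is collected only to make the assessment systematic.

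**The concern.** Testing is not randomised and has no fixed threshold. It is prompted by the impression that the participant has worsened, and that impression plausibly predicts readmission. This is confounding by indication. No adjuster named in the article measures the indication, because the examples given describe the participant as known at discharge.

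The response adds a second difficulty. The visit can lead straight to readmission, so a test that detects a problem and prompts readmission counts against testing. Readmission alone is therefore a poor measure of what a test contributed.

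The measure also departs from its own purpose. The label speaks of decision making, and Data collection speaks of results and decisions. Table 2 uses the conduct of a test in place of its result, and one late consequence in place of the range of decisions. At stake is the reading of a secondary outcome: a useful test could be reported as associated with more readmissions, or a useless one as protective, depending on how the comparison is set up.

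**Working it through.** The article gives no figure for Outcome 6, so there is none to reproduce. The one figure borrowed is the intervention-arm readmission risk in Sample power and statistical power: 19% × (1 − 0.28) = 13.68%. All other inputs are assumptions.

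**Model among visited participants.** A share w of visits raises concern. Testing is done in a share t1 of visits with concern and t0 of visits without. Concern multiplies readmission risk by RRw, and testing multiplies it by RRt.

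- Relative risk level, tested: RRt × [w·t1·RRw + (1−w)·t0] / [w·t1 + (1−w)·t0]
- Relative risk level, untested: [w·(1−t1)·RRw + (1−w)·(1−t0)] / [w·(1−t1) + (1−w)·(1−t0)]
- The crude RR is the first divided by the second. The overall risk cancels.

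**Base case**, w = 0.30, t1 = 0.80, t0 = 0.10, RRw = 2, RRt = 1:
- Tested: (0.24×2 + 0.07)/0.31 = 1.774
- Untested: (0.06×2 + 0.63)/0.69 = 1.087
- Crude RR = 1.63 with no effect of testing. Scaled to 13.68% overall, that is 18.7% v 11.4%.

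**Range.** The grid has w = 20, 30, 40%; t1 = 60, 80, 100%; t0 = 0, 10, 20%; and RRw = 1.5, 2, 3, 4, which is 27 scenarios for each RRw. RRt = 0.72 borrows the design's 28% as an assumed benefit of testing; the article makes no such claim for testing alone.

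| RRw | Base case, RRt = 1 | Grid, RRt = 1 | Base case, RRt = 0.72 | Grid, RRt = 0.72 | Share of grid above 1, RRt = 0.72 |
|---|---|---|---|---|---|
| 1.5 | 1.33 | 1.15–1.50 | 0.96 | 0.83–1.08 | 37% |
| 2 | 1.63 | 1.29–2.00 | 1.18 | 0.93–1.44 | 89% |
| 3 | 2.17 | 1.52–3.00 | 1.56 | 1.09–2.16 | 100% |
| 4 | not run | 1.71–4.00 | not run | 1.23–2.88 | 100% |

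The crude RR exceeds the true RRt in every scenario, so the bias is upward throughout. Whether the result lies above 1 is not fixed.

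**If the whole intervention arm is used.** Background gives a median of nine days to readmission, and the visit falls 2–5 working days after discharge, so some readmissions precede any test. Those participants would enter as untested with an event. Suppose 25% of 30-day readmissions come before the visit, with base-case values, RRw = 2 and RRt = 1:
- Early events: 0.1368 × 0.25 = 0.0342. Visited: 1 − 0.0342 = 0.9658.
- Risk after the visit: 0.1026/0.9658 = 0.1062. Baseline: 0.1062/1.30 = 0.0817.
- Tested: 0.0817 × 1.774 = 0.145.
- Untested: (0.0817 × 0.75 × 0.9658 + 0.0342)/(0.69 × 0.9658 + 0.0342) = 0.0934/0.7006 = 0.133.
- Crude RR = 1.09, against 1.63 among visited participants only.

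| Share readmitted before the visit | RRt = 1 (RRw 1.5, 2, 3) | RRt = 0.72 (RRw 1.5, 2, 3) |
|---|---|---|
| 10% | 1.15, 1.40, 1.82 | 0.84, 1.02, 1.34 |
| 25% | 0.91, 1.09, 1.38 | 0.68, 0.82, 1.05 |
| 40% | 0.70, 0.82, 1.02 | 0.53, 0.63, 0.79 |

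A test with no effect can thus appear harmful or protective according to the analysis set.

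**The case against.** The protocol claims little. Table 2 speaks of an association, and the Discussion concedes more than once that the elements of the intervention cannot be separated. Statistical analyses leaves the regressions to a research statistician, and the listed risk factors are only examples, so an unseen analysis plan could add condition at the visit. Data collection already points to results and decisions. All of this stands and limits the weight of the point. It does not rescue the stated measure, which fixes both exposure and response and serves an aim framed as the value of testing.

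A reader might infer three stronger things that the documents do not support:
- That the analysis is bound to make testing look harmful. The sign depends on the true benefit, on how strongly concern predicts readmission, and on an analysis set that the article does not state.
- That there are no untested participants with the same concern. The Abstract leaves testing to discretion, and under Intervention blood tests and the scan are a further, optional step. Such participants may be few for vital signs, where concern is the stated trigger, but they are allowed for.
- That the measure contains no decision at all. Acute readmission is one decision that the visit can produce. It is an incomplete proxy for decision making, and the link from test to readmission is a bias only if the regression is read as the effect of testing.

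**Conclusion.** The point holds in limited form. As written, Outcome 6 is confounded by indication, and it does not match its own label or the purpose given under Data collection. Among visited participants the expected bias is towards harm: crude RRs run from 1.15 to 4.00 when testing does nothing, and from 0.83 to 2.88 when it truly lowers risk by 28%. Counting early readmissions as untested pulls these down, below 1 in some cases even with no effect. These ranges rest on assumed shares of concern, testing rates and prognostic strength; they show direction and possible size and do not forecast the result. They are crude ratios, and adjustment for condition at the visit would reduce the bias to an unknown extent. This concerns one secondary outcome. The randomised comparison of 30-day readmission is not touched.

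**What to change.** Reword the measure for Outcome 6:
- Restrict it to participants who received the visit.
- Make the exposure the measurement or POCT result among those tested.
- Make the response the decision at the visit, as far as it is recorded: care-plan adjustment, video consultation, outpatient assessment or acute readmission.
- Drop the regression of readmission on whether a test was conducted, or keep it as descriptive, with follow-up from the visit and a statement that it supports no inference about the effect of testing.

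The cost is mainly wording. Data collection says that visit data, including vital signs and POCT results, are registered, and Intervention says that care-plan adjustments are noted. Video consultations and outpatient referrals are not shown to be recorded as fields. Since the trial began in November 2022, the response may have to be limited to what exists. The outcome becomes more descriptive: it will show how results went with decisions among those tested, and it will not show whether testing prevents readmission.

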### Data collection

Data will be collected at several points. The data will all be saved and stored in a secure database (REDCap). All personnel involved will be trained data collection.

Before the participant is invited to join the study, data is gathered on eligibility (i.e. diagnosed moderate to severe dementia, residence location to identify citizens of Odense Municipality, and type, use of home care, terminal diseases and presence of delirium).

Before discharge, data is gathered from the participants’ electronic medical records regarding discharge diagnoses, LOS, medication, medical history and Barthel ADL score [39]. A Clinical Frailty Score [40] is assessed by a geriatric nurse.

All data collected during the follow-up visit is registered in our database, including the data gathered in the FS-III survey, vital status and POCT results. The vital parameters and POCT results will be used to understand their influence on the clinical decision making.

The data collected during the follow-up visit will be filled directly into pre-defined fields in REDCap and will help ensure that all the necessary data is collected.

All participants, controls and interventions will receive a questionnaire, which is a modified version of a previously validated questionnaire [41]. At the time of randomisation, both groups will be asked about their satisfaction with the treatment, care and hospitalisation in general, as well as if they feel safe being discharged. A follow-up questionnaire will be administered to both groups by telephone. Data will be transferred to REDCap manually. The questionnaires will be administered by project coordinators who are not involved in the clinical care of the patients.

Data on death and readmissions will be collected from electronic medical records for 1 year after the allocation date for each participant.

### Data analyses

#### Sample power and statistical power

Based on our recent finding of a 28% reduction in readmissions following geriatric follow-up to discharged geriatric patients [42], and using a 2-proportions with 2-sample equality power test, a current readmission rate of 19% (control group), and an expected 28% reduction by the intervention, the readmission rate in the intervention group is (19 − (19 × 0.28)) 13.68%. If the proportions of group A, *pA*, is (100 − 19 =) 81 and proportion of group B,* pB*, is (100 − 13.68 =) 86.32,* α* = 0.05,* β* = 0.80 and* К* = 1, the sample size should include 763 in each group, and 1526 patients totally [43]. The total finally becomes 1832 after accounting for an expected dropout rate of 20%. The Department of Geriatric Medicine at Odense University Hospital is expected to discharge about 1500–1800 patients in 2022–2023 alone, which makes it feasible to include enough participants to reach statistically significant results in 2 years. We had originally calculated a shorter time period for the study, however, due to COVID and nurse shortage, the number of beds has been reduced. We have included statistics for all inclusion and exclusion criteria in our model for estimation of the time required for the study.

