### Study design

The study is a single-centre two-arm parallel group randomised controlled trial with an aim to show superiority. It will utilise permuted block randomisation without stratification. Distribution will be equivalent between the two groups. The study will be conducted over approximately 24 months.

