### Statistical analyses

Statistical analyses will be carried out STATA Version 17 (StataCORP LLC, Texas, USA).

We will exclude participants with single-item missing data relevant to the analysis and will not perform imputations. An intention-to-treat analysis will be employed to maintain the integrity of our results. A per-protocol analysis will also be performed to complement the primary intention-to-treat analysis. While the intention-to-treat analysis preserves the advantages of randomisation and reflects real-world implementation challenges, the per-protocol analysis may help assess the true effect of receiving the intervention as intended. Given the negligible planning costs and absence of adverse effects, the intervention may still be considered clinically relevant even if statistical significance is only observed in the per-protocol population.

Characteristics will be reported with numbers, percentages and means with standard deviations or medians with interquartile range, as appropriate. Differences will be calculated using appropriate tests. Appropriate regression analyses will be conducted according to advice from a research statistician. Threshold for significance will be *P* < 0.05.

Readmission and mortality will be calculated and compared as relative risks. We will conduct an interim analysis after 1 year to adjust the time length of the study and to assure that one group does not have a significantly higher mortality rate or readmission rate than the other, which are the stopping criteria. The outcomes examined in the interim analysis will be 30-day mortality and 30-day readmission rate. The interim analysis will be conducted on data masked by a third party to ensure blinding, and the data will not be unblinded unless there is a significant difference in mortality, which is the only stopping criteria. The interim analysis will be conducted after 13 months have passed, i.e. January 2024.

The financial costs analyses will be conducted under supervision of a health economist, [name]. We will analyse our data including time spent by the health professionals and estimate intervention cost per participant, which will be compared to an estimated daily cost of admission and the estimated avoided readmission days.

Qualitative analysis will be conducted to assess user perspectives. This will be conducted as a separate parallel study by [name] [name].

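### The 20% dropout allowance is applied as ×1.2 instead of ÷0.8, so 1832 enrolled leaves about 1466, not the 1526 required

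*Protocol article*

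**What the plan says.** All references are to the protocol article.

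- **Sample power and statistical power.** The calculation is described as "using a 2-proportions with 2-sample equality power test", with "a current readmission rate of 19% (control group), and an expected 28% reduction by the intervention". From these, "the readmission rate in the intervention group is (19 − (19 × 0.28)) 13.68" per cent. The result is 763 per group and 1526 in total. The section then adds: "The total finally becomes 1832 after accounting for an expected dropout rate of 20" per cent. It does not say what counts as dropout.
- **Study design.** On allocation: "Distribution will be equivalent between the two groups".
- **Statistical analyses.** "We will exclude participants with single-item missing data relevant to the analysis and will not perform imputations". The same paragraph makes intention-to-treat the primary analysis, with a per-protocol analysis alongside it.
- **Data collection.** "Data on death and readmissions will be collected from electronic medical records for 1 year after the allocation date for each participant".
- **Analyses of primary and secondary outcomes.** The 30-day acute readmission rates are compared by relative risk. Patient characteristics such as multimorbidity, polypharmacy and length of stay are to be included in the analyses.

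**The concern.** A dropout rate is a share of the people enrolled. To keep a required number after losing a fraction d, the required number is divided by 1 − d. Multiplying by 1 + d gives too few, because the loss also falls on the participants added to cover it. The stated total matches the multiplication.

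If so, the recruitment target does not deliver the evaluable number, or the 80% power, that the same paragraph promises under its own dropout assumption. The paragraph also leaves the meaning of dropout open, although the primary outcome is read from records and need not be lost when someone misses a visit or a questionnaire.

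**Working it through.** **Inputs**

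- Control rate p1 = 0.19 and intervention rate p2 = 0.19 − 0.19 × 0.28 = 0.1368 (Sample power and statistical power).
- α = 0.05 (same section; the analysis threshold agrees: "Threshold for significance will be *P* < 0.05"). Sidedness is not stated; two-sided is assumed.
- Power 0.80. The article labels this value β, but its sample size is reproduced only when 0.80 is the power.
- Allocation 1:1 (Study design). Dropout d = 0.20.

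**Step 1: reproduce 763 per group**

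Difference: 0.19 − 0.1368 = 0.0532. Variance sum: 0.19 × 0.81 + 0.1368 × 0.8632 = 0.2720. Mean rate: 0.1634, so 2 × 0.1634 × 0.8366 = 0.2734.

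- Unpooled: n = (1.960 + 0.842)² × 0.2720 / 0.0532² = 754.3, that is 755.
- Pooled: n = (1.960 × √0.2734 + 0.842 × √0.2720)² / 0.0532², which gives 758.

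Both lie within 3% of 763. A continuity correction gives 795 and a one-sided test 597, so neither explains 763. The evaluable target of 1526 is accepted.

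**Step 2: reproduce 1832**

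- 1526 × (1 + 0.20) = 1831.2, rounded up to 1832. This matches exactly.
- 1526 / (1 − 0.20) = 1907.5, rounded up to 1908. This is 76 more (76 / 1832 = 4.1%), too large a gap for rounding.

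**Step 3: what 1832 leaves after 20% loss**

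- 1832 × 0.80 = 1465.6, about 1466, or 733 per arm.
- Shortfall: 1526 − 1466 = 60.
- Largest loss that still leaves 1526: 1 − 1526 / 1832 = 16.7%.

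**Step 4: power**

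Pooled form: power = Φ[(0.0532 − 1.960 × √(0.2734 / n)) / √(0.2720 / n)].

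| Analysed per arm | Situation | Power, pooled | Power, unpooled |
|---|---|---|---|
| 763 | required number | 80.3% | 80.4% |
| 733 | 1832 enrolled, 20% lost | 78.7% | 78.9% |
| 916 | 1832 enrolled, none lost | 86.9% | 87.0% |

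The inflation error costs 80.3 − 78.7 = 1.6 points. Against the nominal 80%, the gap is 80 − 78.7 = 1.3 points, because 763 is slightly above the 758 that the pooled formula needs.

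**The case against.** **The effect is trivial.** A gap of 1.3 to 1.6 points is small beside the uncertainty in the assumed 28% reduction. This stands as a limit on the importance of the point. It does not make 1832 the right figure for a 20% dropout rate.

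**The 20% may have been meant as a top-up.** The addition is 1832 − 1526 = 306, which is 20% of 1526 but 16.7% of 1832. If the authors meant extra recruits equal to 20% of the evaluable number, the arithmetic is consistent. But the text calls it an expected dropout rate, and 1832 does not cover that rate.

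**Loss may be lower than 20% anyway.** Readmission comes from electronic records for each participant, and the intervention is one visit. If loss stays at or below 16.7%, 1832 is enough. This is correct, and it is why the fix does not ask for more participants. The article should then say so, since its stated assumption is 20%.

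**A stronger reading is tempting.** A reader might infer that the missing-item exclusion rule removes further participants beyond the 20% and breaks intention-to-treat for the primary outcome. The article does not support that:

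- It never says what the 20% covers, so these exclusions may already be inside it.
- It gives no rate of missing items, so no further loss of power can be calculated.
- The rule applies only to data relevant to the analysis in question. For an unadjusted relative risk of readmission, a missing questionnaire or Barthel score is not relevant.
- Nothing in it drops people who decline the visit.
- The covariates named as examples are of a kind available from hospital records.

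What remains is that the rule may remove some randomised participants from covariate-adjusted analyses, by an unknown number. That is a separate matter from the arithmetic, and the choice of imputation method is partly preference.

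**Conclusion.** The point holds for the inflation step. The total of 1832 comes from multiplying by 1.2; the figure that matches a 20% loss is 1908. Under the article's own assumptions, 1832 leaves about 1466 participants, 60 short of 1526, with about 78.7% power instead of the stated 80%. The total is sufficient only if loss is no more than 16.7%.

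This rests on a two-sided 5% test, 1:1 allocation, 0.80 read as power, the rates of 19% and 13.68%, and dropout read as a share of those enrolled. The arithmetic is certain and the consequence modest. It does not show that the trial is materially underpowered, nor that the primary analysis departs from intention-to-treat.

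**What to change.** 1. In Sample power and statistical power, keep 1832 and state that it leaves the required 1526 if loss is at most 16.7%, and gives about 79% power if loss reaches 20%. If the authors prefer a total that matches a 20% allowance, that total is 1908. Raising the target is hard to justify when the Eligibility and Trial status sections report too few eligible patients.
2. Add one sentence on the primary analysis set: every randomised participant whose records can be read is kept in the intention-to-treat relative risk for 30-day readmission, whether or not the home visit, the questionnaire or a baseline covariate is complete. Say in the same place what the 20% dropout is meant to cover.
3. State that the missing-item exclusion rule can affect covariate-adjusted analyses only, and report how many participants it removes from each.

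The cost is one restated figure and two or three sentences, with no added enrolment or data collection. The stated power becomes slightly less favourable at 20% loss. If record-based follow-up keeps actual loss for the primary outcome well below 20%, that power is recovered, up to about 87% if all 1832 are analysed.
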